### Data management

2.5

Data management uses EXCEL software to build a database, double entry, check for outstanding values, and lock. Information obtained from the evaluation of each participant will be recorded on a paper print-out. The information will then be handwritten on a paper document case report form and entered into an Excel file for future statistical analyses. In accordance with the Personal Information Protection Act, the names of all participants will not be disclosed, and a unique identifier number given during the trial will be used to identify participants. All of the participants will be informed that the clinical data obtained in the trial will be stored in a computer and will be handled with confidentiality. The participants’ written consent will be stored by the principal investigator. (Fig. 2)

**Figure 2 F2:**
[figure not shown]
Study design flow chart.

### Ethics

2.6

The study will be conducted under the Declaration of Helsinki principles, as well as following the norms of good clinical practice. Recruitment of patients has not started in this study. The study plan will be submitted to the ethics committee of the Kailuan General Hospital for review. The study protocol will be approved by the ethics committee of Kailuan General Hospital. The protocol of this study has been registered in the Chinese Clinical Trial Registry with the number ChiCTR2000034177.

## Discussion

3

China is a country with a high incidence of periodontal disease, 80% to 90% of adults suffer from varying degrees of periodontal disease.^[10]^ According to the results of the third national oral health epidemiological survey in 2000, the number of patients with periodontitis in urban and rural areas in China is as high as hundreds of millions.^[11]^ However, due to poor health awareness and inadequate prevention and early treatment, periodontal diseases have seriously affected the oral health of the Chinese people, and even overall health.^[12,13]^ With the improvement of living standards and lifestyle changes, the incidence of MetS in our country has increased significantly. The prevalence of MetS in the population reaches 25%.^[14,15]^ As an independent risk factor for various diseases, MetS has begun to attract people's attention for its role in the occurrence and development of periodontal diseases. The cause of MetS is not yet clear. It is currently believed to be the result of the interaction of multiple genes and multiple environments, and is closely related to genetics and immunity.^[16]^ The disease is affected by a variety of environmental factors, and is concentrated in a high-fat, high-carbohydrate diet structure, increasing the occurrence of insulin resistance, low labor intensity, and low physical activity resulting in the occurrence and development of MetS.^[17]^ The main clinical manifestations of MetS are abdominal obesity or overweight, abnormal lipid metabolism, hypertension, diabetes, insulin resistance and/or abnormal glucose tolerance.^[18]^ The main clinical manifestations of periodontal disease are gingival inflammation, bleeding, periodontal pocket formation, alveolar bone resorption, alveolar bone height reduction, tooth loosening, displacement, and weak chewing. In severe cases, the teeth may fall off or cause tooth extraction.^[19]^ May have complications such as pain, pus, and bad breath. Local complications of periodontal disease include periodontal abscesses and loose teeth. Systemic effects are generally small.^[20]^ Some scholars believe that it may be related to certain rheumatic diseases. Chronic inflammation develops gradually with repeated episodes. Clinically, it is mainly characterized by alveolar bone absorption and loosening of teeth. It gradually causes occlusal trauma and displaces the teeth.^[21]^ Finally, it causes missing teeth and poor support of the remaining teeth, resulting in difficulties in repair and treatment. At present, there are multiple classification methods for periodontal disease, but it is mainly divided into gingivitis, periodontitis, periodontal trauma, juvenile periodontitis and periodontal atrophy.^[22]^ Gingivitis is mainly limited to inflammatory lesions of the gum tissue, generally does not involve deep periodontal tissue. Periodontitis is most common in periodontal disease, mainly including gingival redness and bleeding, periodontal pocket formation, periodontal pocket overflowing pus, loose teeth, gingival recession, periodontal abscess and so on.^[23]^ Periodontitis is mainly characterized by the formation of pathological periodontal pockets. Periodontal trauma is a disease in which periodontal support tissue is damaged due to excessive bite pressure or abnormal direction, which exceeds the load that the periodontal tissue can bear. It develops slowly and generally has no obvious symptoms. Sometimes it feels weak to chew, or sometimes there is hidden or dull pain.^[24]^ Juvenile periodontitis is a chronic degeneration of the periodontal tissue that affects most teeth. It is characterized by the fact that most of the patients are younger and the lesions develop rapidly, so that the teeth appear loose, displaced, and periodontal pockets are formed at the early stage of the disease, and then secondary infection. Pathogenic factors may be related to heredity. Periodontal atrophy is mainly a regressive lesion of the gum and alveolar bone tissue. Manifested as gingival recession and exposed neck or root. The main causes of periodontal atrophy are: compression of the gums of the tooth neck on the gums; long-term disuse of the teeth at the site or systemic factors; mechanical stimulation caused by incorrect brushing methods; compression of the gums by the restoration.

This study will explore the correlation between periodontal disease and MetS of coal mine workers. We aim to clarify the role and mechanism of MetS in the occurrence and development of periodontal diseases, guide the prevention of periodontal diseases, and thus reduce the prevalence of periodontal diseases. In addition, this study will help to control the development of periodontal diseases, improve oral health and general health, and reduce the consumption of medical resources caused by periodontal diseases.

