
Periodontal diseases are also part of systemic inflammatory diseases. Among Chinese middle-aged and elderly patients with MetS, periodontal morbidity is very high. This is due to the involvement of inflammatory mediators in the pathogenesis of MetS and periodontal disease. The latter may also be a risk factor for the former's morbidity and promotion of disease progression. At present, there are not many investigations involving periodontal examination data and periodontal disease prevalence of patients with MetS. However, there are no domestic reports on coal mine workers, especially those working underground. This study will explore the relationship between MetS (including management personnel, uphole workers, and downhole workers) and explore the significance of MetS in the occurrence and development of periodontal disease, and investigate and analyze in different positions and different jobs Differences in morbidity in the environment. We will hope to provide a reference for the prevention and treatment of periodontal diseases.

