### Participants

2.2

The subjects of this study will be included in the outpatient and hospitalized patients from the Kailuan general hospital, and meet the diagnostic criteria for MetS.

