#### Inclusion criteria

2.2.2

This study will be conducted in China. Patients will be recruited from Plastic surgery departments of the Kailuan general hospital. We will enroll participants based on the following inclusion criteria:

(1)Meet the diagnostic criteria of Western Medicine MetS.(2)Occupation is coal mine employees (including management personnel, underground workers, underground workers).(3)The age is between 20 to 55 years old.(4)Those who have voluntarily signed the informed consent;

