### Interventions

2.3

We will collect the clinical diagnosis and treatment information of the enrolled patients (such as symptoms, syndromes, signs, electrocardiogram and laboratory examination data, physical examination data, and so on). We will focus on checking the incidence of periodontal disease and recording. Establish a database, check every 10 medical records, and make corrections in time to ensure data accuracy. First of all, we will popularize oral hygiene knowledge for the included patients and guide them to brush their teeth correctly and use dental floss. We will perform periodontal examination on the patients’ teeth by site and record the plaque index, gingival sulcus bleeding index periodontal pocket exploration depth and other indicators. After the inspection, the periodontal pockets were rinsed with 3% hydrogen peroxide solution and 0.9% sterile saline. We will repeat the above inspection items and record in the second and fourth weeks of the experiment. None of the patients in the 2 groups received systemic antimicrobial therapy, and the above clinical operations were performed by the same doctor.

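### The aim (role and mechanism of MetS in the occurrence of periodontal disease) and the focus on incidence exceed what the design can show

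*Protocol article*

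**What the plan says.** The purpose is worded in three ways.

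- **Correlation.** The last paragraph of the Discussion opens with "This study will explore the correlation between periodontal disease and MetS of coal mine workers".
- **Cause and mechanism.** The next sentence of that paragraph reads "We aim to clarify the role and mechanism of MetS in the occurrence and development of periodontal diseases", and goes on to prevention and lower prevalence. The Introduction has a similar purpose, to "explore the significance of MetS in the occurrence and development of periodontal disease".
- **Incidence.** Section 2.3 (Interventions) says "We will focus on checking the incidence of periodontal disease and recording".

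On who is studied, section 2.2 draws on "outpatient and hospitalized patients from the Kailuan general hospital, and meet the diagnostic criteria for MetS". The first inclusion criterion in section 2.2.2 is "Meet the diagnostic criteria of Western Medicine MetS". The inclusion and exclusion criteria say nothing about periodontal status at entry.

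On follow-up, section 2.3 has participants taught oral hygiene and examined, with the pockets then rinsed with hydrogen peroxide and saline. It continues: "We will repeat the above inspection items and record in the second and fourth weeks of the experiment". The same section mentions two groups without defining them.

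**The concern.** Occurrence and incidence refer to new disease in people who were free of it. Role and mechanism refer to cause. To support such aims, a study needs participants at risk at the start, a known order of exposure and outcome, variation in the exposure, and enough observation time not altered by treatment. The article describes none of these for MetS and periodontal disease.

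If the aim stays as worded, existing disease found at the first examination may be reported as incidence. Any association may then be read as evidence that MetS brings on or advances periodontal disease, and be used to guide prevention. No result of this design would justify that reading.

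**Working it through.** The article gives no sample size, effect size or onset rate, so there is no figure of its own to reproduce. The check sets each element of the aim against the design, with one small calculation.

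**1. Occurrence and incidence.** Only people without the disease at entry can become new cases.

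- Inputs: prevalence of about two thirds (Introduction) and 80% to 90% of adults (Discussion). These are figures for the general population of China. Applying them to participants is an assumption.
- Formula: share at risk = 1 − prevalence.
- Results: 1 − 2/3 = 33%; 1 − 0.80 = 20%; 1 − 0.90 = 10%.

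So about 10 to 33 of every 100 enrolled would be at risk. The share could be lower here, because the Introduction describes periodontal morbidity as very high in middle-aged and elderly patients with MetS.

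As an illustration only, take an annual onset rate r among those at risk. The article gives none, so r = 0.02 to 0.20 per year is an assumption. New cases per 100 enrolled over 28 days = 100 × (1 − prevalence) × (1 − exp(−r × 28/365.25)).

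| Prevalence | At risk per 100 | New cases, r = 0.02 | New cases, r = 0.20 |
|---|---|---|---|
| 2/3 | 33.3 | 0.05 | 0.51 |
| 80% | 20.0 | 0.03 | 0.30 |
| 90% | 10.0 | 0.02 | 0.15 |

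Across that range, at most about one new case per 200 enrolled would be expected. What the first examination finds is existing disease, which is prevalence.

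**2. Development (progression).** The indices are recorded three times: at the first examination and in weeks 2 and 4. Hygiene teaching is planned for the included patients, and rinsing follows the examination. No untreated comparison is described. Change from the first examination therefore mixes the course of disease with the effect of these measures, and the two cannot be separated.

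**3. Direction.** MetS is an entry condition, and periodontal status is first recorded after entry. Which came first is unknown for every participant. The Introduction says of periodontal disease that "The latter may also be a risk factor for the" former, meaning MetS. The article thus names the reverse pathway while aiming at only one direction.

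**4. Role of MetS itself.** Sections 2.2 and 2.2.2 both require MetS, so MetS present versus absent does not vary among the participants described. Without that variation its association with periodontal disease cannot be estimated, even cross-sectionally. What does vary is which MetS components are present and how severe they are, and job category.

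**5. Analysis.** Section 2.4 names a chi-square test between groups and a model relating syndromes to clinical indicators. Neither is an analysis of onset, and neither would supply the missing time order.

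**The case against.** The best defence is that this is loose wording. The title and the first sentence of the Discussion's closing paragraph frame the study as correlational. The Discussion also uses incidence when citing the 80 to 90% figure, which is a prevalence, so section 2.3 probably means the number of participants found to have the disease. That is a fair reading of the word. It still leaves the outcome misnamed in the methods, and it does not cover role, mechanism, occurrence and development, which are written as aims in two sections.

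A reader might infer more than the text supports:

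- **That the article concludes that MetS causes periodontal disease.** It does not. The causal statement is an aim, and no result is claimed.
- **That status is examined only once.** There are three examinations; only status at entry rests on one.
- **That mechanism fails because no inflammatory mediator is measured.** The lists of data in sections 2.3 and 2.4 are open-ended and include laboratory data, and the article is a condensed account. The absence of a named mediator proves nothing. The case against a mechanistic aim rests on time order and on the lack of variation in MetS.
- **That the design at least supports a cross-sectional association of MetS, present versus absent, with periodontal disease.** As described it does not, because everyone has MetS. The two groups might have been meant to include workers without MetS, but the text does not say so, and it would conflict with the inclusion criteria.

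**Conclusion.** The concern holds as a mismatch between the stated aim and outcome and the design described. Incidence, direction and mechanism cannot be established. The data can support the prevalence and severity of periodontal disease at the first examination among coal mine workers with MetS, their cross-sectional relation to MetS components and job category, and short-term change after the local measures.

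On size, by the article's own population figures about 10 to 33% of participants would be free of disease at entry, provided that participants resemble that population. The four-week case counts depend on assumed onset rates and serve only as illustration. The conclusion does not need them, because it follows from the entry criteria, the unknown time order and the treated follow-up. The point should be corrected, and section 2.6 says that recruitment has not started.

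**What to change.** - **Aim (Introduction and Discussion):** restate it as estimating the prevalence and severity of periodontal disease at the first examination among coal mine workers with MetS, and their cross-sectional association with MetS components and job category.
- **Aim wording:** remove role, mechanism, occurrence and development as things that the study sets out to establish. They may remain as background.
- **Section 2.3:** replace incidence with prevalence. Describe the week 2 and week 4 data only as short-term change after the hygiene teaching and rinsing.
- **Limits:** state that direction and cause cannot be inferred, and that the article itself considers both directions plausible.
- **Groups:** define the two groups. Unless one is specified as workers without MetS, with the entry criteria changed to match, claim no association of MetS itself with periodontal disease.

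Apart from the optional addition of a group without MetS, these are changes of wording that need no new data. The cost is a less favourable claim: the study would describe disease burden and its correlates in workers with MetS, and would give weaker grounds for advice on prevention. Adding a group without MetS would require further recruitment, and it would still give only a cross-sectional association.
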